# Primary percutaneous stenting above the ampulla versus endoscopic drainage for unresectable malignant hilar biliary obstruction (TESLA RCT): study protocol for a multicenter randomized controlled trial

**DOI:** 10.1186/s12885-025-14158-0

**Published:** 2025-05-09

**Keywords:** Malignant hilar biliary obstruction, Primary percutaneous stenting, Endoscopic biliary drainage, Randomized controlled trial, Major complications, Overall survival

## Abstract

**Background:**

Patients with malignant hilar biliary obstruction typically present with painless jaundice. They commonly have perihilar cholangiocarcinoma (pCCA), but also intrahepatic cholangiocarcinoma, gallbladder cancer, and metastases to the liver hilum can present with hilar biliary obstruction. Endoscopic biliary drainage is the standard of care in most centers. Many patients develop drainage-related complications after endoscopic biliary drainage for malignant hilar biliary obstruction, in particular cholangitis, resulting in reinterventions, clinical deterioration and a high mortality rate. Primary percutaneous stenting (PPS) aims to avoid bacterial contamination and reduce drainage-related complications. The aim of this randomized controlled trial is to compare PPS with endoscopic biliary drainage in patients with unresectable malignant hilar biliary obstruction.

**Methods:**

This multicenter phase 3 randomized controlled trial (TESLA RCT) will recruit 148 patients with unresectable malignant hilar biliary obstruction in six Dutch tertiary academic referral centers. Diagnosis of malignant hilar biliary obstruction is pathologically confirmed or determined as very likely by the multidisciplinary team. In the intervention arm, patients undergo primary percutaneous stenting with uncovered self-expandable metal stents without crossing the ampulla and without leaving an external drain. In the control arm patients undergo endoscopic biliary drainage according to international guidelines. The primary endpoint is major complications within 90 days after randomization. Secondary outcomes include technical success, reintervention rates, decrease of bilirubin levels, eligibility for palliative systemic treatment, quality of life, and overall survival.

**Discussion:**

The multicenter TESLA RCT compares primary percutaneous stenting with endoscopic biliary drainage in patients with unresectable malignant hilar biliary obstruction. First patient was randomized on August 9, 2023.

**Trial registration:**

Netherlands Trial Register (NL-OMON53463), registered on May 12, 2023, and Clinicaltrials.gov (NCT06671418), registered on November 1, 2024.

## Background

Malignant hilar biliary obstruction (MHBO) is most commonly caused by perihilar cholangiocarcinoma (pCCA), but can also be caused by intrahepatic cholangiocarcinoma, gallbladder cancer, and metastases from other malignancies to the liver hilum [1, 2]. Most patients with MHBO are ineligible for curative surgery due to the presence of distant metastases, locally advanced disease or poor performance status. In the palliative setting, the median overall survival of pCCA is approximately 5 months [3–5]. Painless jaundice is the typical presentation in patients with unresectable MHBO. Adequate biliary drainage is a prerequisite for effective palliative care including quality of life improvement and palliative systemic treatment [6]. The standard of care for palliative biliary drainage is through endoscopic retrograde cholangiopancreatography (ERCP) with plastic or self-expandable metal stents (SEMS; Fig. 1a). When ERCP has failed or is not feasible due to anatomical challenges (e.g., after a gastric bypass), percutaneous biliary drainage (PBD) is the preferred intervention (Fig. 1b) [7]. 

The main drawback of both ERCP and PBD is the high incidence of drainage-related infections caused by bacterial contamination of the biliary tract. This contamination is probably caused by the transpapillary approach followed by stents often placed across the ampulla, or internal-external bile duct drains placed percutaneously. Inadvertent instrumentation or contrast injection into undrained liver segments increase the risk of segmental cholangitis requiring reinterventions and often results in clinical deterioration. Consequently, most patients with unresectable MHBO never get systemic treatment and survival remains poor [4, 8, 9]. In a Dutch nationwide study of 186 patients with perihilar cholangiocarcinoma, 161 patients underwent ERCP and 24% of these patients required unplanned reintervention. The 90-day mortality of the entire cohort (ERCP and PBD) is 36%. Notably, no difference in 90-day mortality was found between initial ERCP and PBD [10]. In another cohort of 16.822 patients from the UK patients who underwent palliative PBD for biliary tract cancer had a median overall survival of 92 days after drainage [11]. 

We hypothesize that the poor outcomes of PBD and ERCP shown in prior studies are mainly due to bacterial contamination of the bile ducts caused by disruption of the ampulla. Primary percutaneous stenting (PPS) aims to maintain the sterility of the bile ducts as it avoids crossing the ampulla. The stents only cross the biliary duct obstruction with the distal end of the stent placed in the extrahepatic bile duct. By glueing the puncture trajectory after PPS the need for an external drain is omitted (Fig. 1c). This technique was investigated in our single center TESLA pilot study (MEC-2019-0789) of 67 patients with unresectable MHBO [12]. Cholangitis or pancreatitis were never observed after the initial PPS in all 67 patients. Other drainage-related severe complications were observed in only 17.9% and all were resolved with reinterventions; two patients (3.0%) developed acute cholecystitis, one patient (1.5%) a biliary leak, three patients (4.4%) hemorrhage, and six patients (9.0%) had persistent jaundice. Most patients (61.2%) started with palliative systemic treatment within four weeks after drainage. Palliative systemic treatment was never withheld due to complications of drainage or inadequate drainage. The median overall survival was 10.1 months (95% CI 7.9–14.4) with a 6-month OS of 68.7% (95% CI 58.4%-80.7%).

To validate the results of the non-randomized pilot study, we designed a multicenter, randomized controlled trial, the TESLA RCT. This study has been registered at Netherlands Trial Register (NL-OMON53463) and ClinicalTrials.gov (NCT06671418). The primary aim of this study is to determine whether PPS reduces major complications compared to ERCP in patients with unresectable MHBO.

**Fig. 1 Fig1:**
[figure not shown]
(**A**) Endoscopic biliary drainage (ERCP); (**B**) Percutaneous biliary drain (PBD); (**C**) Primary percutaneous stenting (PPS)

## Methods

### Trial design

The TESLA RCT is a multicenter, phase 3, randomized controlled trial. All six Dutch academic centers treating patients with primary liver tumors have agreed to participate. Patients with unresectable MHBO are randomized for PPS with uncovered self-expandable metal stents (ucSEMS) without crossing the ampulla and without leaving an external drain (intervention; arm 1) or ERCP according to the American Society for Gastrointestinal Endoscopy (ASGE) guidelines of 2021 (control; arm 2). Randomization is performed in a 1:1 ratio using type of tumor (pCCA versus other types of malignancies) and center of inclusion as stratification factors through the web-based software tool for clinical research CASTOR EDC (version 2023.1.0.0). All participating centers must perform five PPS procedures in the TESLA pilot before participating in the TESLA RCT to minimize the impact of a potential learning curve for the intervention arm.

### Trial eligibility

Patients with unresectable MHBO and hyperbilirubinemia > 50 µmol/L (> 2.8 mg/dL) are screened for inclusion. All patients are discussed in a multidisciplinary team in an academic center to confirm ineligibility for both liver resection and liver transplantation. Unresectability can be due to local tumor extension (i.e., locally advanced disease), distant metastases, insufficient future liver remnant (FLR) function due to liver parenchyma disease, and/or poor patient performance. Ineligibility for liver transplantation is based on international guidelines [13]. Written informed consent is obtained. Cytological or histological confirmation of malignancy is recommended. However, study inclusion is also allowed if the multidisciplinary team agrees that the risk of malignancy is very high based on symptoms, imaging, and laboratory values.

Exclusion criteria include a high suspicion of benign disease, for example because of fluctuation or spontaneous decrease in bilirubin levels before the initiation of any treatment or a high IgG4. Previous biliary drainage attempts and clinical signs of cholangitis are other exclusion criteria. Cholangitis is defined as the presence of both fever (i.e., body temperature ≥ 38.5 °C) and leukocytosis (i.e., ≥ 10 × 10^9^/L) without clinical or radiological evidence of acute cholecystitis [14]. Patients who underwent an attempted, but failed ERCP are eligible only when no papillotomy or cannulation was performed.

### Treatment

In both treatment arms, the objective is to drain > 50% of non atrophic liver (ASGE guideline 2021) [4, 8, 9, 15]. A low threshold for placing more than one stent is recommended. Drainage of atrophic liver segments and liver segments with portal vein occlusion is avoided. Both procedures are performed under deep sedation with propofol and anesthesiologic monitoring.

### Intervention arm: PPS

After sterile exposure, percutaneous ultrasound- and fluoroscopy-guided access to the biliary tree is obtained (Fig. 2A-D). When pathological confirmation is lacking, percutaneous or endoluminal forceps biopsy or brush cytology is performed. Before stent insertion, the stricture is dilated with a balloon catheter of 6–8 mm that is pulled over the guidewire, as shown in Fig. 2E. Bilateral stenting involves kissing percutaneous transluminal angioplasty (PTA) with 6 mm. After balloon dilatation, an ucSEMS is placed ensuring adequate overlap with the unaffected bile ducts and without crossing the ampulla. After stent placement, post-dilation with a 6 to 8 mm kissing balloon catheter is conducted (Fig. 2F-G). The percutaneous transhepatic puncture tract is sealed with 0.5 gr Avitene™ (BD, NJ, USA) mixed with 8 ml of iodine contrast agent without leaving an external drain, as shown in Fig. 2H. Passing of the tumor may require several attempts and considerable time. Only when the tumor cannot be passed with a wire after repeated and prolonged attempts, an external biliary drain is placed. A second attempt of recanalization and stenting is performed after 3 to 5 days.

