### Primary and secondary endpoints

The primary endpoint of this study is the proportion of patients with major complications within 90 days after randomization. Major complications are defined as any complication leading to prolonged hospital stay of more than 72 h; readmission to a hospital; any invasive reintervention, and/or death, within 90 days after randomization. Major complications include drainage-related complications (Table 1) and complications that do not appear to be drainage-related.

Secondary outcomes include primary and secondary technical success of stent placement at the initial drainage procedure, the number of reinterventions, admission days after drainage, patient-reported quality of life, bile cultures at initial drainage, and primary clinically successful drainage. Other secondary outcomes were the proportion of patients that started with palliative systemic treatment, 90-day mortality, and OS. Primary technical success was defined as successful passage of the stricture and stent placement without leaving an external drain during the initial drainage procedure. Secondary technical success was defined as successful passage of the stricture and stent placement during a second attempt 4–7 days after an unsuccessful initial procedure. Primary clinically successful drainage was defined as a bilirubin 50 µmol/L (> 2.8 mg/dL) or a reduction in bilirubin level of at least 50% within 14 days after the first drainage procedure.

**Table 1 Tab1:** Definitions of severe drainage-related complications

Complication	Criteria
Cholangitis	Elevation in temperature ≥ 38,5 °C and Leukocytes ≥ 10 *10^9^/L, thought to have a biliary cause and requiring invasive intervention, without concomitant evidence of acute cholecystitis.
Acute cholecystitis	Radiologic evidence of cholecystitis, elevation in temperature more than 38.5 °C and Leukocytes ≥ 10 *10^9^/L, requiring emergency cholecystectomy or percutaneous drainage.
Persistent jaundice	Persistent elevated bilirubin levels after primary technically and clinically successful drainage had initially been obtained, without signs of cholangitis or cholecystitis, requiring a reintervention.
Acute pancreatitis	Two or more of the following criteria be met for the diagnosis of acute pancreatitis: abdominal pain suggestive of pancreatitis, serum amylase or lipase level greater than three times the upper normal value, or characteristic imaging findings.

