#### Sample size calculation

The sample size calculation was conducted for the primary outcome. The major complication rate in the control arm (ERCP) was estimated at 50% based on the literature. To detect a 50% reduction in the complication rate (to 25%) with 90% power and a 5% two-sided significance level, and with one non-binding interim analysis for superiority, a total of 148 patients will need to be randomized. The sample size calculation was performed using East software (version 6.5, Cytel Inc., Cambridge, MA). The estimated accrual period is three years. Total study duration is 3.5 years with 6 months follow-up after inclusion of the last patient.

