PPS as an alternative to ERCP and PBD aims to prevent bacterial contamination of the biliary tract. This approach was investigated in the TESLA pilot study (MEC-2019-0789) involving 67 patients with MHBO and without prior drainage attempts (i.e. uncolonized biliary tract). Most patients were diagnosed with perihilar cholangiocarcinoma (40.3%), followed by intrahepatic cholangiocarcinoma (34.3%), gallbladder cancer (13.4%), liver metastases (10.5%), and hepatocellular carcinoma (1.5%). PPS showed a technical success rate of 98.5% at the initial procedure. Severe drainage-related complications occurred in 17.9% of patients. There were no cases of cholangitis or pancreatitis observed. Complications included acute cholecystitis (3.0%), biliary leak (1.5%), hemorrhage (4.4%), and persistent jaundice requiring additional stenting (9.0%). No drainage-related mortality was reported. Palliative systemic treatment was initiated in 62.7% of patients, and the median overall survival was 10.1 months (95% CI 7.9–14.4) [12]. (TESLA pilot study, submitted) The single-center and single-arm setting may limit the reproducibility of the TESLA pilot study. The participating interventional radiologists have specific expertise on treatment of hilar obstructions which may have had a favorable impact on the outcome. Comparisons with historical ERCP and PBD data may underestimate the quality and outcomes of the current procedures. Especially ERCP outcomes may have improved over time due to novel approaches such as suprapapillary stenting and centralization. Prior research has shown that SEMS placement is associated with lower stent failure rates compared to plastic stents in patients with resectable perihilar cholangiocarcinoma, potentially contributing to drainage outcomes [24]. 

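### The second PPS attempt may fall on day 3, but secondary technical success only counts from day 4, so an on-schedule day-3 success has no success category

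*Protocol article*

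**What the plan says.** Under Intervention arm: PPS, the protocol article describes what follows when the stricture cannot be crossed: "Only when the tumor cannot be passed with a wire after repeated and prolonged attempts, an external biliary drain is placed". The timing of the repeat procedure comes next: "A second attempt of recanalization and stenting is performed after 3 to 5 days".

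Under Primary and secondary endpoints, primary and secondary technical success are named as secondary outcomes and each is defined. Primary technical success is "successful passage of the stricture and stent placement without leaving an external drain during the initial drainage procedure". Secondary technical success is "successful passage of the stricture and stent placement during a second attempt 4–7 days after an unsuccessful initial procedure".

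The first window governs treatment in the PPS arm and the second governs how the outcome is classified. Nothing in the article reconciles them.

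**The concern.** An endpoint window should at least cover the days on which the protocol itself tells the operator to act. Here the lower bound of the definition is one day later than the lower bound of the schedule. If a repeat procedure on day 3 succeeds, the analyst has two poor options: apply the written rule and deny credit to a protocol-compliant success, or depart from the definition after seeing the case.

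Only the classification of one secondary outcome is at stake. The primary endpoint (major complications within 90 days of randomization), the sample size, the significance level, primary technical success and the count of reinterventions do not use this window.

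The upper end is not criticised. A definition that runs to day 7 when the schedule ends on day 5 is ordinary tolerance for delay.

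**Working it through.** **Comparing the windows**

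- Scheduled days (Intervention arm: PPS): {3, 4, 5}.
- Days that count (Primary and secondary endpoints): {4, 5, 6, 7}.
- In both: {4, 5}. Scheduled but not countable: {3}. Countable but not scheduled: {6, 7}.

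**Does another category catch a day-3 success?** Primary technical success requires stent placement at the initial procedure and no external drain left behind. The patient who goes on to a second attempt was not stented at the initial procedure and had an external drain placed then. Both conditions fail, so a day-3 success is neither primary nor secondary.

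**How many patients could be affected?** Inputs:

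- Total sample size, from Sample size calculation: "a total of 148 patients will need to be randomized".
- Allocation, from Trial design: "Randomization is performed in a 1:1 ratio". The PPS arm is therefore 148/2 = 74.
- Pilot result, from the Discussion: "PPS showed a technical success rate of 98.5% at the initial procedure". With 67 pilot patients this reproduces as 66/67 = 98.5%, so there was 1 failure.
- Share of second attempts made on day 3, and their success rate: not in the document. Each is allowed to range from 0 to 1.

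Calculations:

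1. Pilot failure rate = 1/67 = 1.49%, with exact (Clopper-Pearson) 95% confidence interval 0.04% to 8.04%.
2. Expected second attempts = 74 × failure rate. At the pilot rate, 74 × 1/67 = 1.10. At the upper limit, 74 × 8.04% = 5.9.
3. Probability of at least one second attempt at the pilot rate = 1 − (66/67)^74 = 1 − 0.329 = 0.67.
4. Expected number misclassified = expected second attempts × share on day 3 × success rate:

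| Failure rate | None on day 3 | All on day 3, all successful |
|---|---|---|
| 1.49% (pilot) | 0 | 1.1 |
| 8.04% (upper limit) | 0 | 5.9 |

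5. If technical success is summarised as the proportion of all 74 PPS patients with either primary or secondary success, each misclassified patient lowers it by 1/74 = 1.4 percentage points.

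**The case against.** The case against concedes the mismatch and argues about weight and remedy.

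- **The effect is close to nil.** A patient is misclassified only if the first procedure fails, the repeat falls on day 3 and the repeat succeeds. If days 3, 4 and 5 were equally likely (an assumption), the pilot rate gives at most 1.10/3, or about 0.4 patients. This stands and is why the point is minor. The pilot rate may be optimistic, though: the Discussion itself warns that a single centre with specially experienced operators may not be reproducible, and six centres now take part.
- **The figure of 5.9 stacks extremes.** It does. It is an outer bound, not an expectation.
- **The 1.4-point shift uses a combined proportion the article does not define.** Correct. With only failed first procedures in the denominator, the shift per patient would be different. The figure holds only for the combined proportion over 74 patients.
- **Other repairs would work, and a change in both arms reaches further than the mismatch.** Moving the schedule, or counting any second attempt, would also close the gap. The article gives no second-attempt timing for endoscopic drainage, so the effect of a day-3 start in the control arm cannot be judged from it. However, the definition is already written without reference to arm. Correcting it in one place keeps it common to both and avoids changing treatment.
- **The article condenses a fuller protocol.** That would excuse an omission. It does not excuse two stated windows that disagree.

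**Conclusion.** The concern holds, as a minor internal inconsistency. Both windows are in the current text, both count from the first procedure, and they leave day 3 scheduled but unclassifiable as a success.

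The plausible size is about one patient or fewer in the PPS arm at the pilot failure rate. This rests on carrying a single-centre rate over to six centres and on a day-3 share that the article does not report. No effect on the primary comparison and no bias between arms has been shown.

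**What to change.** In Primary and secondary endpoints, start the secondary technical success window at day 3, so that it covers a second attempt 3 to 7 days after an unsuccessful initial procedure, and apply it identically in both arms. Leave the 3 to 5 day schedule under Intervention arm: PPS unchanged. Every on-schedule success then has a category, and the tolerance up to day 7 is kept.

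The cost is one number in one sentence. Treatment, sample size and power do not change. Randomization began in August 2023, so the change should be documented and dated as an amendment to an outcome definition, preferably before results are seen by arm. Cases already recorded can be reclassified from procedure dates, provided those dates were captured.

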**Fig. 2 Fig2:**
[figure not shown]
Step by step process of primary percutaneous stenting. Ultrasound-guided access to the biliary tree is obtained (**A**); and fluoroscopy confirms catheter placement in the bile duct (**B**); Contrast injection visualizes the biliary anatomy and obstruction (**C**); A guidewire is advanced, carefully passing the tumor while avoiding the ampulla (**D**); Balloon dilation is performed to widen the stricture (**E**); and stent insertion is performed, followed by post-dilation with two balloon catheters (**F**); Bilateral uncovered self-expanding metallic stents are deployed (**G**); and the puncture tract is sealed with Avitene (**H**)

### Control arm: ERCP

ERCP is performed by a gastroenterologist who is experienced in performing ERCP in patients with MHBO. ERCP is performed according to the ASGE guidelines of 2021 [4, 8, 9, 15]. 

### Periprocedural care

#### Antibiotics

All patients receive a single intravenous dose of cefuroxime 1500 mg with metronidazole 500 mg during procedure. After the drainage procedure, all patients receive another five-day course of broad spectrum antibiotics (i.e., amoxicillin-clavulanic acid or ciprofloxacin). If bilirubin levels exceed 250 µmol/L (15 mg/dL) before procedure, its recommended to start prophylactic oral broad spectrum antibiotics at diagnosis to prevent spontaneous cholangitis prior to biliary drainage.

